**Methodology**

**Study aim and objectives**

This study is order to provide a new therapeutic method for patients with myocardial ischemia-reperfusion injury and reveal the possible mechanism of ECSW for ischemia-reperfusion injury.

The objectives of the study as follows:

**I.** The primary endpoint of this study is 2-year all-cause death, rehospitalization due to cardiovascular disease, major adverse cardiovascular and cerebrovascular events, including cardiac death, myocardial infarction, heart failure, arrhythmia, emergency coronary revascularization, and stroke;

**II.**Secondary endpoints are improvement in angina, quality of life, cardiac structure and function, coronary microcirculation, and expression level of endothelial progenitor cell-derived miR-140-3p.

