**Randomization**

Patients with acute ST-elevation myocardial infarction reperfusion who met the inclusion criteria and signed an informed consent will be randomized by coin toss. With the coin heads up, patients with acute ST-elevation myocardial infarction reperfusion will be assigned to the extracorporeal shock therapy group. With the coin heads down, patients with acute ST-elevation myocardial infarction reperfusion will be assigned to a blank control group.The test group and the control group will be divided into 1:1 proportional grouping. In order to ensure blinding, the details of the random assignment will not be given to the investigator. In addition, Shock wave treatment practitioners and evaluators will be completely separated.

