**Study intervention**

The experimental group will be given extracorporeal cardiac shock wave therapy 2 - 3 days after PCI for acute myocardial infarction, and the treatment course is 3 months. 9 treatments were completed within 3 months as 1 treatment course, 1 week per month, 3 weeks rest, and 3 times of extracorporeal cardiac shock wave will be performed in each treatment week, respectively on the 1st, 3rd, and 5th days of the treatment week, lasting for 3 months in total; The control group received conventional treatment for acute myocardial infarction.

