The experimental group meeting the inclusion and exclusion criteria will be treated by the external cardiac shock therapy instrument in accordance with standard operating procedures, specifically to determine the treatment target myocardium: according to the conventional left ventricular myocardium will be divided into 17 segments, through load ultrasound or load nuclide myocardial perfusion imaging, combined with ECG, coronary angiography and other results, to determine the therapeutic bullsey-eye muscle segments. Vital signs monitoring: During treatment, patients will be required to lie in a quiet position, and 12-lead combined electrocardiogram (ECG) will be recorded, connected to ECG, blood pressure and oxygen saturation monitoring. Setting the height of the water sac: Adjust the height of the water sac (positioning) according to the location of the target myocardium before positioning, and then move the ultrasonic probe down and slightly protruding from the surface of the water sac to achieve clear positioning. After positioning, it is appropriate to increase the height of the water sac until the patient's chest wall is lightly touched but not compressed, in order to reduce the energy attenuation in the process of seismic wave conduction. Airborne ultrasonic detection of bull's eye muscle segments: When the probe moves down and touches the chest wall, the left ventricular long axis image will be displayed first, and then the ultrasonic adjustment button will be rotated clockwise to display the left ventricular short axis, four chambers and two chambers of the left heart section in turn. When more than two sections lock the same segment together, the positioning will be regarded as successful. Energy control: Raise the probe after positioning so as not to interfere with shock wave release. Then press the shock wave releaser, starting from a small energy level of 0.8 (equivalent to 0.024 mJ/mm2). The successful release is marked by the occurrence of "Da, da" sound consistent with the patient's heart rate. Every 200 points is one frequency cycle. If there is no special, the energy level can be gradually adjusted to level 3 (0.09 mJ/mm2); Fine-tuning of treatment points in the target area: under normal circumstances, we will line a combination of 9 points between 1 ~ 0 ~ -1 or 2 ~ 0 ~ -2 for each area, and issue 200 pulses at each point, giving a total of 1800 pulses (9×200). Monitoring during treatment: ask patients about their symptoms and observe their vital signs and electrocardiogram. In case of discomfort or changes in electrocardiogram, lower the energy level first and continue to observe, treat as appropriate, record and analyze the causes in detail.

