
**Data collection and follow-up**

All necessary data will be collected and recorded in electronic case report forms for this study, which will be mainly obtained from medical records(such as electronic or paper medical records), local laboratory testing records and investigator’s evaluation on patients. Relevant baseline data will be collected at the time of enrollment in patients with acute ST-segment elevation myocardial infarction reperfusion, mainly including:demography(age, gender, race), medical history, signs, treatment, biochemical values(mainly including serum electrolyte value, serum AST, serum ALT, serum creatinine, serum BUN, serum CK-mb, cTNI, BNP and HsCRP), imaging examination indicators(Echocardiography will be used to measure left ventricular ejection fraction (LVEF), left ventricular end diastolic diameter(LVEDD), global longitudinal strain, myocardial stress changes in each segment and synchrony of myocardial motion, left ventricular contrast echocardiography will assess coronary microcirculation), relevant scale scores(mainly will include 6-minute walk test, Canada Cardiovascular Society (CCS) angina classification, Seattle angina scale (SAQ) score, quality of life scale (SF-8)) (Appendix D) and expression level of miR-140-3p in endothelial progenitor cell (EPCs)-derived exosomes in peripheral blood;Biochemical values, imaging parameters, scores of relevant scales, expression level of miR-140-3p in endothelial progenitor cell (EPCs)-derived exosomes and major adverse cardiovascular events (which will include all-cause death, readmission due to cardiovascular disease, cardiac death, myocardial infarction, heart failure, arrhythmia, emergency coronary revascularization and stroke) will be collected in the test group and control group at 1, 4, 6, 12 and 24 months.

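### Arrhythmia is a primary event without any threshold, and only the shock-wave arm has nine ECG-monitored sessions, so it may be detected more often in that arm.

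*Protocol*

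**What the plan says.** **Endpoint.** Under Study aim and objectives the protocol states: "The primary endpoint of this study is 2-year all-cause death", followed by cardiovascular rehospitalization and major cardiovascular and cerebrovascular events, "including cardiac death, myocardial infarction, heart failure, arrhythmia, emergency coronary revascularization, and stroke". Data collection and follow-up repeats the list, again with arrhythmia unqualified: "heart failure, arrhythmia, emergency coronary revascularization and stroke". That section collects events in both arms at 1, 4, 6, 12 and 24 months. The data come mainly from medical records, laboratory records and the investigator's evaluation.

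**Treated arm.** Under Study intervention, patients "will be given extracorporeal cardiac shock wave therapy 2 - 3 days after PCI", and "9 treatments were completed within 3 months as 1 treatment course" (three sessions in one week of each month). At a session, "12-lead combined electrocardiogram (ECG) will be recorded, connected to ECG, blood pressure and oxygen saturation monitoring". Staff are to "ask patients about their symptoms and observe their vital signs and electrocardiogram". If the ECG changes, the change and its causes are to be documented in detail.

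**Control arm.** Under Randomization, these patients "will be assigned to a blank control group". Study intervention gives them conventional treatment. No sham session or matching monitored contact is described.

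**Safeguard.** Randomization separates the people who deliver the treatment from those who evaluate patients.

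**The concern.** Whether an arrhythmia is found depends on how often someone looks at the ECG. Here one arm is looked at on nine extra occasions, in the first three months after infarction. Because the component has no threshold, a brief asymptomatic rhythm finding could be read as a primary event with the same weight as a death.

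A difference in looking would then appear as a difference in outcome. The bias would run against the shock-wave therapy. The hypothesis is that the therapy reduces clinical endpoints, so the risk is that a real benefit is hidden or that harm appears where there is none. Neither the sample size nor the log-rank and Cox methods under Data analysis can correct for this, because the error lies in which events are recorded.

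**Working it through.** **1. The plan's own figure.** The only sample size is for left ventricular ejection fraction: difference 8.1 points, SD 11.7, two-sided alpha 0.05, power 90%.

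n per arm = 2 × (1.960 + 1.282)² × 11.7² / 8.1² = 43.8, so 44 as stated. Then 44 × 1.15 = 50.6, so 51 as stated.

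The figure reproduces but does not bear on this point. The protocol gives no event rate, hazard ratio or event count for the composite.

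**2. Scheduled contacts, from the text.**

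| | Shock-wave | Control |
|---|---|---|
| ECG-monitored sessions, months 0–3 | 9 | 0 |
| Common visits, months 0–3 | 1 | 1 |
| Common visits, months 0–24 | 5 | 5 |
| Total, months 0–24 | 14 | 5 |

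The items listed for the common visits do not name an ECG.

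**3. Illustration with a true benefit.** The inputs are assumptions, not protocol figures: control 2-year rate 30%, true hazard ratio 0.70, and probability p per session of an arrhythmia recorded only because of the session.

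- True treated rate = 1 − 0.70^0.70 = 22.1%, a benefit of 7.9 points.
- Extra detection over nine sessions = 1 − (1 − p)^9.
- Observed treated rate = 1 − (1 − 0.221) × (1 − p)^9.

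| p per session | Extra over 9 | Observed treated rate | Observed benefit |
|---|---|---|---|
| 0.5% | 4.4% | 25.5% | 4.5 points |
| 1% | 8.6% | 28.8% | 1.2 points |
| 2% | 16.6% | 35.0% | −5.0 points |

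The benefit vanishes when (1 − p)^9 = 0.70 / 0.70^0.70 = 0.70^0.30 = 0.8985, that is at p = 1.2%.

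If routine inpatient monitoring equalised detection in the first treatment week (also an assumption), six sessions would remain. Then 1% per session gives 26.7% (benefit 3.3 points) and 2% gives 31.0% (benefit gone). The break-even rises to 1.8%.

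**4. Illustration with no true effect.** Assume control rates of 20% to 40%, 51 per arm, and a share e of otherwise event-free treated patients who gain a session-only event. The observed treated rate is pc + (1 − pc) × e. The test is a two-sided 5% comparison of two proportions with pooled variance. For example, pc = 30% and e = 10% give 0.30 + 0.70 × 0.10 = 37%, a risk ratio of 1.23 and rejection in 11.6% of trials.

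| e | Observed risk ratio | Two-sided rejection |
|---|---|---|
| 0 | 1.00 | 5.0% |
| 5% | 1.07–1.20 | 6.1–7.7% |
| 10% | 1.15–1.40 | 9.3–15.6% |
| 20% | 1.30–1.80 | 22.7–43.5% |

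Most of the rejections are in the direction of harm. With a true risk ratio of 0.5, e = 10% moves the observed ratio to 0.70–0.95 and cuts power for benefit from 29–60% to 3–25%.

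**The case against.** The strongest reply is that no text sends session findings into the endpoint. Arrhythmia is listed among major adverse events, which argues against counting trivial findings. Endpoint data are collected at the same five visits in both arms, treaters and evaluators are separated, and an SAP that is not shown may define the event. It stands that a reader may not infer that every rhythm abnormality at a session counts, or that detection will be higher. The protocol supports only that it may be. The reply does not close the gap. Events are drawn from medical records, one arm generates more ECG records, and an evaluator kept apart from treatment still reads those records. A later definition could narrow the component, but the unequal monitoring is fixed in this protocol.

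The figures are also open to challenge. They treat sessions as independent although they cluster within a week and within a patient. They treat session findings as unrelated to events the patient would have had anyway, and they allow no offsetting detection in controls. Each of these tends to enlarge the effect. At 1% per session the excess is 6.7 points, about 3.4 of 51 patients, which does not swamp the serious events. Only the 2% case reverses the direction.

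Inpatient monitoring after PCI may cover both arms early on. The protocol does not say so, and six of the nine sessions fall in later months. Study setting and subjects places the intervention in the outpatient clinic.

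Finally, an arrhythmia provoked by the treatment is a real effect and not a detection artefact. That is correct, and any fix must keep such events.

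**Conclusion.** The point holds as a risk of arm-dependent detection in the primary endpoint. It rests on four features of the text: an arrhythmia component without a threshold, nine ECG-monitored sessions in one arm only, a control arm without matching contacts, and no rule on session-only findings. The direction, if the bias occurs, is against the therapy. The size is unknown. The range of 25.5% to 35.0% against a true 22.1% illustrates what assumed rates would do and is not an estimate.

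Three stronger readings are not supported:

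- **That the trial could not be read whatever its result.** A benefit shown despite this bias would be conservative and still readable. The difficulty is with a null or harmful result.
- **That heart failure shares the flaw because patients may enter in NYHA class I to III.** That range applies to both arms, and the protocol shows no arm difference in how heart failure is ascertained.
- **That rehospitalization needs the same change.** No arm difference in its ascertainment is shown either.

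**What to change.** Amend the endpoint wording under Study aim and objectives and under Data collection and follow-up:

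1. Count an arrhythmia as a primary event, in either arm, only if it presents clinically. This means that it leads to unplanned admission, prolongs a current hospital stay, needs treatment or resuscitation, or causes death.
2. State that such an event counts if it occurs during or after a session, so that harm provoked by the treatment stays in the endpoint. The clause on prolonged stay matters because sessions start 2 to 3 days after PCI. A patient still in hospital could have a serious non-fatal arrhythmia without any new admission.
3. Report asymptomatic ECG findings seen only at shock-wave sessions, and not meeting this definition, in a separate safety table.
4. Add a sensitivity analysis of the composite that counts all recorded arrhythmias, so that readers can see how far the result depends on the definition.

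The change needs no extra procedures or staff. The cost is somewhat fewer primary events. It removes most of the asymmetry but not all, since an arrhythmia treated only because a session monitor showed it would still count.

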**Research hypothesis**

We hypothesized that extracorporeal cardiac shock therapy would also be effective in reducing clinical endpoints in patients with STEMI reperfusion.

**Study design**

This is a single-center, prospective randomized controlled trial to investigate the clinical efficacy of in vitro cardiac shock wave therapy in patients with myocardial ischemia-reperfusion injury, the difference in the level of endothelial progenitor cell derived miR-140-3p between the shock wave treatment group and the control group, and the relationship between the expression level of miR-140-3p and clinical efficacy and prognosis. In order to provide a new therapy for patients with myocardial ischemia-reperfusion injury. Participants will be patients with first-time acute ST-segment elevation myocardial infarction who have undergone percutaneous coronary intervention (PCI) within 12 hours of onset according to current guidelines for revascularization and have had no major adverse clinical events in the past 6 months. A thorough explanation of the study by using the information sheet (Appendix A) will be provided to all eligible participants and informed consent also will be obtained from the participants before the commencement of the study (Appendix B).

**Study setting and subjects**

The study protocol and implementation will have complied with the principles of Declaration of Helsinki^7^. Firstly, The study will be approved by the Ethics Review Committee of the First Affiliated Hospital of Kunming Medical University. Permission will also be obtained from the Director of the First Affiliated Hospital of Kunming Medical University. Secondly, the purpose of the study, the data collection procedures, the potential risk and benefits, the maintenance of confidentiality, and the voluntary basis of participation will be clearly explained to the participants. Participants will be informed that they have the choice to withdraw from the study at any time if they choose to do without penalty or negative consequence of current health services.

Thirdly, the informed consent will be provided in written and oral form when the research personnel approaches the potential participants. The detailed information and explanation of the nature of the study, the right of participants to withdraw from the study at any time, the anonymity and confidentiality of the participants, contact details of the researcher which participants may contact to obtain further information if they need will be included in the subject information sheet. Fourthly, to maintain the anonymity of the participants, they will be asked not to write their name in the questionnaire, however, the code number will be provided by the researcher. All data will be kept by the principal investigator in a password-protected computer and a locked cabinet to ensure the confidentiality of participants. The participants will be informed that all personal data will only be accessed by the principal investigator and all the collected data will be destroyed five years after the study completion.

This study will be conducted in the First Affiliated Hospital of Kunming Medical University. The study site is a 4,000-bed hospital serving more than 40 million people in Yunnan Province and neighboring regions. Most acute myocardial infarction patients in Yunnan province will receive treatment at the hospital. Study participants will be recruited from study hospital wards. The intervention will be performed at the hospital's cardiology outpatient clinic. The hospital provides multidisciplinary services, including cardiologists, doctors, nurses and other health care workers. The flow chart for the main study is shown in Appendix C.

**Inclusion and exclusion criteria**

The eligibilities of participants are; ≥18 years old; Acute ST-segment elevation myocardial infarction was diagnosed for the first time, and coronary angiography indicated moderate to severe coronary artery stenosis. PCI was performed within 12 hours of the onset of the disease according to the current guidelines, and the postoperative hemodynamics were stable; CCS angina pectoris grade Ⅱ and above, NYHA cardiac function grade I-Ⅲ; Imaging examination [stress echocardiography and/or stress myocardial perfusion imaging] suggested objective evidence of reversible myocardial ischemia; Voluntary participation, able to cooperate with treatment and follow-up, signed informed consent.

Exclusion criteria will include: unprotected severe left main disease; Left ventricular systolic function was impaired and hemodynamic instability was observed. Poor sound window in ultrasound examination due to chronic obstructive pulmonary disease, bullae, pseudobreast implantation or other reasons; Combined with breast malignancy; Pregnancy; Treatment area skin ulceration or infection; NYHA cardiac function grade Ⅳ; Acute myocarditis, pericarditis, moderate or large pericardial effusion, infective endocarditis, deep vein thrombosis, intracardiac thrombus; Severe aortic stenosis, aortic aneurysm, thoracic aortic dissection, thoracic aortic aneurysm, heart transplantation, metal heart valve replacement, pulmonary embolism; Patients undergoing thrombolysis and surgical bypass; Patients with a history of mental illness, poor compliance and inability to cooperate.

**Randomization**

Patients with acute ST-elevation myocardial infarction reperfusion who met the inclusion criteria and signed an informed consent will be randomized by coin toss. With the coin heads up, patients with acute ST-elevation myocardial infarction reperfusion will be assigned to the extracorporeal shock therapy group. With the coin heads down, patients with acute ST-elevation myocardial infarction reperfusion will be assigned to a blank control group.The test group and the control group will be divided into 1:1 proportional grouping. In order to ensure blinding, the details of the random assignment will not be given to the investigator. In addition, Shock wave treatment practitioners and evaluators will be completely separated.

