**Sample size estimation**

This study is a randomized controlled trial. The experimental group will be received extracorporeal cardiac shock wave therapy intervention, while the control group will be received conventional treatment for acute myocardial infarction. The left ventricular ejection fraction (LVEF) of the study object is one of the observed outcome indicators. According to the literature review results, the average LVEF in the control group is 58.0 ± 11.7 points. It is estimated that LVEF in the shock wave intervention group can be increased by 8.1%,α= 0.05, and the assurance is 90%. Calculate the sample size according to the following sample size calculation formula

[figure not shown]

44 cases can be calculated, considering 1:1 randomization, that is, 44 cases in the intervention group and 44 cases in the control group, and considering 15% will lost to follow-up and refuse to visit, finally, at least 51 subjects in the intervention group and 51 subjects in the control group will be needed, and a total of at least 102 subjects will be included.

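### Allocation rests on a manual coin toss with no stated concealment procedure, custodian or audit trail; 51 per arm at 102 patients is also not guaranteed

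*Protocol*

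**What the plan says.** The Randomization section of the Protocol fixes the allocation method. Patients who meet the criteria and have given "informed consent will be randomized by coin toss". The coin decides the arm patient by patient: "With the coin heads up, patients with acute ST-elevation myocardial infarction reperfusion will be assigned to the extracorporeal shock therapy group", and with heads down the patient "will be assigned to a blank control group".

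The same section promises a ratio: "The test group and the control group will be divided into 1:1 proportional grouping". Sample size estimation then sets the numbers: "at least 51 subjects in the intervention group and 51 subjects in the control group will be needed", or 102 or more in total.

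Two sentences act as safeguards. One reads "In order to ensure blinding, the details of the random assignment will not be given to the investigator". The other reads "Shock wave treatment practitioners and evaluators will be completely separated".

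The sections on sample size and on the intervention make clear that controls receive usual infarct care. No sham procedure is described. The trial has one centre (Study design).

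**The concern.** Random allocation protects a comparison only if the person enrolling cannot influence which arm a patient enters, and if someone can later confirm that the generated assignment was the one used. A hand-tossed coin produces each assignment on the spot. Unless the toss is witnessed or logged by someone independent, an unwelcome result can be tossed again or passed over, and nothing is left to compare with the arm the patient ended up in.

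Enrolling staff will know each patient's prognosis. Angina class, NYHA class and ischaemia imaging are eligibility criteria, and LVEF is measured at baseline. One exclusion criterion, on compliance and cooperation, calls for judgement. Selection at this step would affect every between-group comparison in the Data analysis section, and analysis cannot reliably undo it.

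The second strand is arithmetic. Independent tosses fix the ratio only on average, whereas the Protocol also states a grouping of 1:1 and a minimum per arm.

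**Working it through.** **Inputs.** All are from the Protocol, Randomization and Sample size estimation: fair coin, 1:1, control LVEF 58.0 with SD 11.7, increase of 8.1, α 0.05, power 90%, 15% loss, at least 51 per arm and 102 in total.

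**1. The plan's own figure.** n per arm = 2 × [11.7 × (1.960 + 1.282) / 8.1]² = 43.85, so 44. This needs 8.1 read as absolute points and a two-sided α; read as a relative increase (0.081 × 58.0 = 4.7 points) it would give 131. Then 44 × 1.15 = 50.6, so 51. The stated 44 and 51 are reproduced.

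**2. Safeguards side by side with what allocation needs.**

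| Needed | What the Protocol gives |
| --- | --- |
| Eligibility and consent settled first | Yes: the patients tossed for are eligible and consented; no statement that this is recorded before the toss |
| Next assignment unpredictable | Yes, for an honest toss |
| Result kept from those enrolling | Asserted, as a blinding measure; no procedure |
| Independent person generates or holds the sequence | Not stated; no list exists before the toss |
| Record against which an assignment can be checked | Not stated |
| Treaters separate from evaluators | Yes, but this protects outcome assessment, not allocation |

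**3. What undetected redirection could do (illustration; k and the 1 SD deficit are assumptions).** Start at 51/51 with equal mean LVEF. Move k patients whose LVEF is 11.7 points below the mean from shock wave to control. The false difference is k × 11.7 × [1/(51 − k) + 1/(51 + k)], and the chance standard error is 11.7 × √[1/(51 − k) + 1/(51 + k)].

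| k | Split | False difference (points) | Share of 8.1 | Standard error | P(this split or worse, fair coin) |
| --- | --- | --- | --- | --- | --- |
| 2 | 49/53 | 0.48 + 0.44 = 0.92 | 11% | 2.32 | 76.7% |
| 5 | 46/56 | 1.27 + 1.04 = 2.32 | 29% | 2.33 | 37.3% |
| 8 | 43/59 | 2.18 + 1.59 = 3.76 | 46% | 2.35 | 13.7% |

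In each row the false difference is below 1.96 standard errors and the split is unremarkable for a coin. Neither the arm sizes nor a baseline comparison would reliably expose it.

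**4. Arm sizes with 102 fair tosses.** X ~ Binomial(102, 0.5), with SD √102 / 2 = 5.05.

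- P(51/51) = C(102, 51) / 2¹⁰² = 7.9%, so one arm is below 51 in 92.1% of cases.
- P(difference of 10 or more) = 2 × P(X ≤ 46) = 37.3%.
- P(smaller arm below 44, before any loss) = 2 × P(X ≤ 43) = 13.7%.
- P(split worse than 41/61) = 3.7%.
- Expected tosses until both arms reach 51 = 102 × (1 + 0.0788) = 110.0. P(both at least 51) is 61% at 110 patients and 92% at 120.

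**5. What imbalance costs in power for LVEF.** Power = Φ{8.1 / [11.7 × √(1/n₁ + 1/n₂)] − 1.960}.

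| Split | Power |
| --- | --- |
| 51/51 | 93.8% |
| 46/56 | 93.6% |
| 41/61 | 92.9% |
| Average over all coin-toss splits of 102 | 93.6% |
| 44/44 (88 evaluable) | 90.1% |
| Average over all coin-toss splits of 88 | 89.8% |

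The loss is 0.2 points at 46/56 and 0.9 points at 41/61. In information terms, 41/61 is worth 4 × 41 × 61 / 102 = 98 equally divided patients.

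**The case against.** The case for leaving the coin alone has real substance.

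- **A fair coin is true randomisation.** Each toss is independent, so knowing past assignments does not help to guess the next. Permuted blocks are weaker on this point, because in a trial without sham past assignments are visible and the last places in a block may be guessed. This stands, and the fix has to allow for it.
- **A reader might infer that the design cannot deliver 1:1 with 51 per arm.** The text does not support that. A fair coin is 1:1 in expectation, and both 51 and 102 are stated as minimums, so recruiting further is allowed. What holds is that 51/51 at 102 is not guaranteed.
- **A reader might infer that allocation is unconcealed.** The Protocol tosses only after eligibility and consent, and says the details are withheld from the investigator. The fair criticism is that this is asserted without a procedure.
- **A reader might argue that concealment fails because the arm is obvious once sessions start.** That confuses concealment with blinding. What becomes visible after assignment cannot change who had already been assigned. Lack of sham bears on performance and detection bias, a separate matter.
- **A reader might take the control as untreated.** It is not: controls receive usual infarct care, and the blank label can only mean no shock wave.
- **Silence is not proof that tosses go unrecorded.** This is correct. The Appendix C flow diagram was not legible in the text examined and could add detail.

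None of this supplies the missing element: a stated way to show that the first toss for each patient was the one acted on.

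**Conclusion.** The concern holds in this form. The Protocol fixes a manual coin toss and asserts concealment without giving a procedure, an independent custodian or an audit trail. A repeated or disregarded toss would leave no trace, so selection bias could not be detected. That is the reason to change it before recruitment. Because the Protocol itself prescribes the method, this is not detail left for a statistical analysis plan.

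The likelihood of subversion cannot be estimated from the documents, and nothing in them suggests that it is intended. The false differences of 0.9 to 3.8 LVEF points rest on the assumed two to eight redirected patients with LVEF one SD low.

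Arm size is secondary. The 7.9% and the expected 110 patients assume a fair coin. The power loss of under 1 percentage point applies to LVEF, on which the sample size is based; the Protocol gives no event rate from which to compute power for the clinical composite.

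**What to change.** Replace the coin toss with a computer-generated 1:1 list in randomly varying, undisclosed block sizes. An existing team member who does not recruit, treat or evaluate prepares it before the first patient. Release one assignment at a time, from sequentially numbered opaque sealed envelopes or a locked file, and only after eligibility and consent have been recorded. Archive the list and a dated allocation log.

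With small blocks (blocks of 4 and 6, for example), 102 patients would split no worse than 50/52. Power hardly changes; the gain is verifiable allocation.

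**Cost.** About an hour of a statistician's time, a one-paragraph amendment and minor envelope or file logistics. There is also a small residual predictability at block ends, because past assignments are visible without a sham. Varying and concealing the block sizes limits it. A pre-generated unrestricted list, kept and released in the same way, avoids it altogether at the price of unequal arms. In that case the 1:1 sentence should be worded as an allocation probability, and the total should allow for reaching 51 in both arms.
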